
### Analysis

#### Statistical analysis will be by the biostatistics team of the Auckland Clinical Trials Research Unit (CTRU)

Data from the trial will be entered into an Oracle database at the CTRU and extracted into SAS for analysis. All statistical analyses will be performed using SAS version 9.2 (SAS Institute Inc. Cary NC). All statistical tests will be two-tailed and a 5% significance level maintained throughout the analyses. Assessment of baseline comparability of the intervention and control group will be carried out via descriptive analyses for demographic information, method of self-harm, and previous history of self-harm. The proportion of people repeating self-harm in each group will be analysed using chi-squared test. We plan to analyse people whose index episode is a first presentation and those whose index is a repeat separately and together. The number of self-harm re-presentation episodes for the hospital and self report outcomes during follow-up will be analysed using negative binomial regression. Kaplan-Meier curves and Cox proportional hazards regression modeling will be used to analyze time to first re-presentation to hospital for self-harm and time to event for the mortality outcomes. The change from baseline to 3 months and one year in each of the repeated continuous outcomes will be analysed using mixed model regression. If baseline characteristics are found to be substantially different between the groups we will adjust for these in the regression modeling. All analyses will be conducted on patients who are randomised and consented except for the re-presentation to hospital and time to re-presentation outcomes which will be an intention to treat analysis that includes all randomised patients including those that did not consent.

In addition sensitivity analyses will be conducted using a CACE analysis [31] where appropriate which takes into account the fact that after randomisation not everyone in a Zelen design agrees to take part in the study. This has the effect of diluting any treatment effect and introducing a possible self selection bias. A CACE analysis is an attempt to correct for this. The assumption behind this is that those who consent to the intervention and treatment as usual are similar. We will test this by comparing the main factors which affect outcomes in both groups including the proportion of people presenting for the first time, gender and age.

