### Randomisation and blinding

As this is a Zelen trial randomisation will be prior to obtaining consent. All eligible participants are allocated randomly to the intervention or usual care groups using a central computerised randomisation system at the Clinical Trials Research Unit (http://www.ctru.auckland.ac.nz). Stratified minimisation randomisation will be used to ensure a balance in key prognostic factors between the study groups: site (Waitemata DHB, Counties Manukau DHB, Northland DHB), history of self-harm (none, repeater), and method of self-harm (overdose, self injury, both). The assessors will be blind to the intervention group at the three and twelve months follow up assessments.

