##### Intervention study

The primary outcome measure is the proportion of subjects who score below nine on the Beck Hopelessness Scale after one year (see sample size section for explanation).

Secondary outcomes are:

1. The proportion of subjects who repeat self harm by presenting to hospital at three months and one year after their index attempt.

2. Self reported repetition of self harm at three months and one year, assessed with a telephone questionnaire and a written questionnaire

3. Hopelessness measured by the Beck Hopelessness Scale at baseline, three months and one year

4. Anxiety and depression measured by the Hospital Anxiety and Depression Scale at baseline, three months and one year

5. Quality of life as measured by the EQ-5D (http://www.euroqol.org/) and the SF36 at baseline, three months and one year

6. Overall mortality (that is suicide deaths plus other causes of death) and suicide deaths at three months, one year, five years and ten years

7. Health service use at three months, one year, five years and ten years, assessed by a telephone questionnaire and interrogation of DHB and Ministry Of Health Information Directorate records

Outcome measures will be collected in several different ways.

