Traditionally the main outcome measure in self harm intervention research has been the proportion of people repeating after one year which is generally around 18% (29). However there are two problems here one of which is particularly relevant for indigenous people. Firstly to significantly reduce this by a third to 12% would need nearly 600 people in each arm of a trial (assuming a power of 80% with a significance level of 0.05). This is particularly problematic in trials involving indigenous people who are less numerous than the majority population. In New Zealand there are about 1000 episodes of self harm involving Māori each year which represents about 840 people. Assuming similar rates of eligibility and recruitment as in the earlier trial this means that the maximum number of Māori who could be enrolled in a treatment trial powered on a significant reduction in the repetition rate is about 300 people a year. In other words a trial would have to involve every DHB in the country and recruit people for four years. We suspect that the chances of funding any such trial are slim. The second problem with repetition rates is that although they are clearly a key consideration they are not important for the four out of five people who do not repeat. Other outcome measures such as measures of distress, quality of life and cultural identity are also significant. For these reasons we have decided that the main outcome we are interested in after one year is the proportion of people scoring below 9 on the Beck Hopelessness Scale. We have chosen this measure for several reasons, it is the best predictor of future self harm attempts; it is a significant marker of distress; and we know from previous research that individuals who score 9 or more on this measure are at least ten times more likely to kill themselves in the next year. Lastly in our previous trial we had outcome data at three months or one year on this scale in 85% of cases. In the previous ACC trial the proportion scoring 9 or more in both groups at baseline was 50%. Using this as the main outcome measure with 80% power, a significance level of 0.05 and a reduction in the proportion scoring above 9 from 50% to 25% after a year will require 66 people in each group, a total of 132. Allowing for 15% non completion of the Beck Hopelessness Scale we will need to recruit 155 people which should be feasible to collect over the fifteen months of recruitment into this trial. The figure of 155 participants is those people who have been randomised and consented to be in the study. We would expect that we would need to randomise about double this number of people to achieve this target.

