##### Analysis

All analyses will be carried out on an intention-to-treat basis for total costs over three months and one year. We will perform multiple regression to adjust for baseline characteristics including age, sex, number of previous attempts and Beck Hopelessness Score. We intend to perform an incremental analysis of costs and consequences using the primary outcome measure as the number of repetitions averted. From this we will produce cost-effectiveness acceptability curves for the intervention.

We also intend to perform a sensitivity analysis to test how the costs and consequences of self-harm change within a range of costs for the different economic inputs. We anticipate that the model will be most sensitive to changes in the costs of in-patient medical care. We will also test the sensitivity of the results to productivity losses and costs of mental health treatment.

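### Covariate adjustment hangs on an undefined baseline imbalance, and the minimisation factors are prespecified in no clinical model

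*Protocol article*

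**What the plan says.** In the Protocol article, the Analysis part of Statistical methods has one sentence on covariates for the clinical outcomes: "If baseline characteristics are found to be substantially different between the groups we will adjust for these in the regression modeling". It sets no threshold, lists no candidate variables and does not say who decides. The regressions named there are negative binomial (number of re-presentations), Cox (time to first re-presentation, mortality) and mixed models. On the last: "The change from baseline to 3 months and one year in each of the repeated continuous outcomes will be analysed using mixed model regression". A chi-squared test is named for the proportion repeating self-harm.

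Randomisation and blinding says: "Stratified minimisation randomisation will be used to ensure a balance in key prognostic factors between the study groups". The factors are site, history of self-harm and method. None is listed as a covariate in a clinical analysis. History is used only to analyse first presenters and repeaters separately as well as together.

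BHS is collected at entry (Table 1). The check of baseline comparability names demographics, method and history, but not BHS or site. The Analysis part of Cost effectiveness analysis, by contrast, fixes its covariates: "We will perform multiple regression to adjust for baseline characteristics including age, sex, number of previous attempts and Beck Hopelessness Score".

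On the primary outcome, Intervention study says: "The primary outcome measure is the proportion of subjects who score below nine on the Beck Hopelessness Scale after one year". The article names no test or model for it.

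**The concern.** A covariate set that depends on how the arms turn out is chosen after the data are seen. Without a threshold, the choice is also discretionary. The trigger looks at the wrong property as well: what makes a covariate worth including is its association with the outcome, and a prognostic factor should be in the model whether or not the arms differ on it.

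Three features of this trial sharpen the point. First, the protocol itself calls the minimisation factors prognostic. Minimising on a prognostic factor and then ignoring it usually gives standard errors that are too large. Second, every outcome except hospital re-presentation and time to re-presentation is analysed in consenting patients only, and about twice as many are to be randomised as consent. Minimisation does not guarantee balance in that subset. Third, the comparability check does not name baseline BHS, so the trigger may never look at a natural predictor of one-year BHS.

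At stake are precision that could be had from data already collected, and protection from a post hoc choice of model.

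**Working it through.** **1. The plan's own figure.** Inputs from Power analysis: "with 80% power, a significance level of 0.05 and a reduction in the proportion scoring above 9 from 50% to 25% after a year", which "will require 66 people in each group, a total of 132". Tests are two-sided at 5%.

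Without continuity correction, with p̄ = 0.375:

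n = [1.96√(2p̄(1−p̄)) + 0.8416√(p₁(1−p₁)+p₂(1−p₂))]² / (p₁−p₂)² = [1.96×0.6847 + 0.8416×0.6614]² / 0.0625 = 57.7, so 58 per arm.

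With continuity correction:

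n′ = (n/4)[1+√(1+4/(n|p₁−p₂|))]² = 14.42×(1+√1.277)² = 65.4, so 66 per arm.

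The stated 66 and 132 reproduce, and 132/0.85 = 155.3 against the stated 155. No covariate enters. At 66 per arm the uncorrected test has power Φ[(0.25√66 − 1.96×0.6847)/0.6614] = Φ(1.04) = 85.1%.

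**2. What adjustment for baseline BHS would add.** Simulation at 66 per arm, 50% v 25%, 4,000 runs per setting. Baseline and one-year hopelessness are latent bivariate normal, and the adjusted test is a logistic likelihood-ratio test. The documents give no correlation, so a range is assumed. Power (%):

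| Correlation | Unadjusted chi-squared | Always adjusted | Adjusted only if baseline differs at p<0.05 | Adjusted only if standardised difference >0.2 |
|---|---|---|---|---|
| 0 | 87.1 | 86.8 | 87.0 | 86.8 |
| 0.3 | 85.8 | 86.9 | 85.8 | 86.2 |
| 0.5 | 86.5 | 90.8 | 87.0 | 88.0 |
| 0.6 | 85.4 | 92.4 | 86.4 | 88.6 |
| 0.7 | 86.4 | 95.6 | 87.7 | 90.6 |

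Monte Carlo error is about 0.55 points. The gain is nil at 0, about 1 point at 0.3, 4 at 0.5, 7 at 0.6 and 9 at 0.7. An imbalance trigger recovers only part of it. Under the null the adjusted test rejected in 5.2 to 6.0% of runs against 4.4 to 5.0% unadjusted, so a little of each gain is test size. The 1 point at 0.3 should not be leaned on.

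**3. What the missing threshold could do.** With either fixed trigger, type I error stayed at about 3 to 5%, so a fixed rule does not inflate it. For correlations 0.3 to 0.7, the adjusted and unadjusted tests disagreed in 2.2 to 6.1% of null trials and 4.5 to 10.6% under the alternative. If the significant result were always chosen, type I error would be (unadjusted + adjusted + discordant)/2: (5.0+6.0+2.2)/2 = 6.6% at 0.3 and (4.7+5.4+6.1)/2 = 8.1% at 0.7.

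**4. Change scores.** With equal variances and correlation r, relative variance is 2(1−r) for change and 1−r² when conditioning on baseline. At an assumed r = 0.5 that is 1.00 v 0.75. If baseline is already a covariate in the mixed model, the two give the same treatment effect.

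**5. Minimisation factors.** The documents give no association between these factors and any outcome, and the simulation did not include them. Only the direction can be stated.

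**The case against.** The strongest objection is that the primary outcome is never assigned to a model. The covariate sentence governs the regression modelling, the regressions listed do not cover a binary BHS endpoint, and primary covariates are ordinary content for an analysis plan that is not shown. This stands. A reader might infer that the primary analysis is an unadjusted chi-squared test, but the article gives that test for repetition of self-harm.

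Other tempting readings also fail:

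- Baseline BHS does not enter the cost regression alone. BHS at baseline, three months and one year is a secondary outcome and falls under the change-from-baseline model.
- The minimisation factors need not look balanced and so drop out. Balance is engineered among all randomised patients, not among consenters.
- An unadjusted one-year proportion is a valid comparison, and it is the quantity on which the trial is powered.

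Two objections bear on the remedy. Patients are randomised, then approached for consent, then given the baseline questionnaires, so baseline BHS is a self-report made after allocation. Adjusting for it could carry bias. That is real, and a sensitivity analysis on the pre-randomisation factors alone answers it. The full model also has seven coefficients besides the intercept (arm 1, BHS 1, site 2, history 1, method 2). With 33 + 16.5 = 49.5 expected scores of 9 or more, that is about 7 per coefficient, which is thin.

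Neither touches the case for removing the trigger or for adjusting for the minimisation factors.

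**Conclusion.** The point holds as a defect in a rule that the protocol states: adjustment in the regression models waits on an undefined imbalance, and the factors used for allocation are prespecified in no clinical model. For the primary outcome the lack of adjustment is inferred from silence.

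The size is modest. At the planned 50% v 25% and 66 per arm, unadjusted power is about 86% (about 81% with continuity correction), so the 80% target is met. A reader might infer an underpowered trial, but the sample size reproduces and what is lost is efficiency. Prespecifying baseline BHS takes power to about 87%, 91% and 92% at assumed correlations of 0.3, 0.5 and 0.6. A reader might also infer an inflated type I error. That would need the favourable model to be picked with results in hand, which the text does not propose; it only leaves room for it.

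The change should be made, but the plan is not invalid without it.

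**What to change.** - Delete the imbalance trigger, or keep it as a labelled sensitivity analysis.
- Prespecify site, history and method as covariates in the negative binomial, Cox and mixed models, and in the comparison of proportions repeating. They are fixed before randomisation, so they are available for non-consenters in the intention-to-treat hospital analyses.
- Analyse continuous outcomes with the baseline score as a covariate.
- For BHS below 9 at one year, prespecify a model with arm, continuous baseline BHS and the three minimisation factors, reported as a marginal risk difference with 95% CI. State in advance how sparse factor categories will be merged.
- Add a sensitivity analysis of the primary outcome with the minimisation factors alone.

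The cost is wording in the analysis plan and one extra model run. No new data and no change in sample size are needed.

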**Methods:**

We propose to use a double consent Zelen design where participants are randomised prior to giving consent to enrol a representative cohort of patients. The main outcome will be the number of Maori scoring below nine on the Beck Hopelessness Scale. Secondary outcomes will be hospital repetition at one year; self reported self harm; anxiety; depression; quality of life; social function; and hospital use at three months and one year.

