### Recruitment

Following a psychosocial assessment by a non-study mental health clinician, patients will be handed a card by non-study clinician which informs them that they will be approached to participate in a study about what happens after self-harm (Additional file 1). If patients do not want to be contacted they will be asked to inform one of the non-study staff. Eligibility for the study will be assessed by a research therapist reviewing the notes. Eligible patients will be randomised and then approached by the research clinician to explain the study and to request consent to participate.

The maximum delay between the psychosocial assessment and the attempt to obtain consent is four days to allow for weekends and public holidays when research staff are not available. In practice we aim to approach potential participants within 24 hours of their presentation to the hospital. The approach will occur either within the Emergency Department, in hospital if the person is admitted, or where necessary, by telephone after the patient is discharged. An interpreter will be made available to any person who requests one.

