##### Ministry Of Health Information Directorate records

we will inspect these for health service use (both general and mental health), repetition and for mortality data. (It is necessary to look at national data on these measures as we found in our previous trial that at least 50% of people who self harm change address over twelve months often outside the DHB where they presented).

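### Mortality, suicide and record-based service use are analysed only in people who consented after allocation, although the same records are already used for everyone randomised

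*Protocol article*

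**What the plan says.** Order of events (Recruitment): "Eligible patients will be randomised and then approached by the research clinician to explain the study and to request consent to participate". The offers then differ. Intervention group describes a six-part package of care; Control group describes usual treatment with questionnaires and interviews.

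Analysis population (Statistical methods, Analysis): "All analyses will be conducted on patients who are randomised and consented except for the re-presentation to hospital and time to re-presentation outcomes". The excepted outcomes get "an intention to treat analysis that includes all randomised patients including those that did not consent".

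Outcomes outside the exception (Intervention study):
- The primary outcome: "The primary outcome measure is the proportion of subjects who score below nine on the Beck Hopelessness Scale after one year".
- Secondary outcome 6: "Overall mortality (that is suicide deaths plus other causes of death) and suicide deaths at three months, one year, five years and ten years". Analysis assigns Kaplan-Meier and Cox methods to "time to event for the mortality outcomes", in the same sentence as time to re-presentation.
- Secondary outcome 7, health service use, taken from a telephone questionnaire and from health board and Ministry records.

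Source of the record-based outcomes (Ministry Of Health Information Directorate records): "we will inspect these for health service use (both general and mental health), repetition and for mortality data". The DHB records paragraph likewise names repetition and service use.

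Analysis acknowledges possible self-selection bias and offers a complier average causal effect (CACE) analysis, where appropriate, as a sensitivity analysis. Separately, the Cost effectiveness analysis section labels its analyses of total costs intention-to-treat.

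**The concern.** Consent here is a post-randomisation event, and agreeing means something different in each arm. Those who accept a therapy package need not resemble those who accept questionnaires alone. Restricting a comparison to consenters therefore gives up the balance that randomisation provides.

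Where an outcome can be found only by asking the patient, the design forces this. Where it can be found in national records, it does not, and the plan shows as much by following non-consenters through those records for re-presentation. Deaths and service use sit in the same sources but get the narrower population. At stake is whether the comparison of deaths, followed to ten years, is a randomised one. The Abstract gives the purpose of the design as follows: "participants are randomised prior to giving consent to enrol a representative cohort of patients".

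**Working it through.** **1. The plan's own figures.** Inputs from Power analysis: 50% v 25% scoring high on the Beck Hopelessness Scale (BHS), power 80%, alpha 0.05; two-sided from Analysis.
- Uncorrected: n = [1.960 × √(2 × 0.375 × 0.625) + 0.842 × √(0.5 × 0.5 + 0.25 × 0.75)]² / 0.25² = 57.7, so 58 per group.
- Continuity-corrected: (57.7/4) × [1 + √(1 + 4/(57.7 × 0.25))]² = 65.4, so 66 per group, 132 in total. This reproduces the stated figure.
- Non-completion of 15%: 132/0.85 = 155.3, stated as 155.

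**2. Who is left out.** Power analysis counts the 155 after consent and expects to randomise about double: 2 × 155 = 310. Those outside the consented set number 310 − 155 = 155, or about half.

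**3. Source against population.**

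| Outcome | Source | Population under Analysis |
|---|---|---|
| Hospital re-presentation, time to re-presentation | Health board and Ministry records | All randomised |
| Overall mortality, suicide | Ministry records | Consenters only |
| Service use, record part | Health board and Ministry records | Consenters only |
| Service use, telephone part | Patient | Consenters only |
| BHS and other scales | Patient | Consenters only |
| Total costs | Interview, routine data, provider finance departments | Labelled intention-to-treat |

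Rows two and three share a source with row one but not its population. Rows four and five cannot be widened. Row six cannot cover all randomised for the interview part, so its label and the rule in Analysis do not agree.

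**4. What moving rows two and three gains.**
- Deaths observed: the Background gives about 1% suicide in the year after self-harm and all-cause mortality that may reach 15% at five years. If these rates apply to everyone randomised, one-year suicides are 0.01 × 310 = 3.1 against 0.01 × 155 = 1.6, and five-year deaths up to 0.15 × 310 = 46.5 against 23.3.
- Power: assume 50% consent, no effect in non-consenters and similar event rates. The contrast is multiplied by 0.5 and its standard error by 1/√2, so the expected test statistic is multiplied by 0.5 × √2 = 0.71. The gain is validity, not sensitivity.

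**5. How far selection could move the primary result (illustration).** Assumptions, none of them from the document: no treatment effect, 40% with BHS 9 or more at one year, no selection among controls, and intervention-arm consent that depends on later hopelessness. The observed intervention proportion is 0.4a/(0.4a + 0.6b), where a and b are the consent rates in those who will and will not be hopeless. Rejection probabilities are exact binomial at 66 per arm.

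| a v b | Observed v control | False difference | Uncorrected test rejects | Continuity-corrected test rejects |
|---|---|---|---|---|
| 60% v 40% | 50.0% v 40% | +10.0 points | 20% | 15% |
| 40% v 60% | 30.8% v 40% | −9.2 points | 20% | 15% |
| 55% v 45% | 44.9% v 40% | +4.9 points | 8% | 6% |
| 45% v 55% | 35.3% v 40% | −4.7 points | 9% | 6% |

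The target effect is 25 points. Similar selection in both arms would largely cancel these differences.

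**The case against.** A reader might infer that the primary comparison should have been intention-to-treat and that the plan chose otherwise. The document does not support that. BHS is self-rated, so people who decline have no score. Analysis discloses possible self-selection bias and never calls the primary analysis intention-to-treat. The article also gives other reasons for the design: a simpler conversation with people in crisis, and avoiding resentful demoralisation among controls. All of this stands.

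It is equally tempting to say that every outcome but re-presentation is restricted. The cost section's intention-to-treat label makes that too broad.

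Nor does weighting consenters on site, self-harm history, method, age and sex solve the primary problem. It removes only the selection that those variables explain, and the illustration above supposes selection on later hopelessness. The illustrated error rates rest on assumed one-arm selection and depend on the test used, so they show what is possible, not what is expected.

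For the record-based outcomes, the defence is that access to deaths and service use of people who declined may go beyond the ethics approval, whose scope the article does not state. That is a proper condition on the change. It does not explain the present text, which already analyses non-consenters' re-presentations. The further defence that including non-consenters dilutes any effect is correct but concerns power, not bias.

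**Conclusion.** The concern holds for overall mortality, suicide and record-based hospital and mental-health service use. The stated rule leaves about 155 of 310 randomised patients out of comparisons that the plan's own sources could make on everyone, with no reason given, and so gives up the randomised comparison for them. The 310 rests on the plan's expectation that about half will consent. The practical gain is small for suicide at one year, with about three expected deaths in all, and larger for all-cause mortality at five and ten years.

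It does not hold as a charge that an all-randomised analysis of the primary outcome was available and passed over. What remains there is a matter of description. CACE cannot correct the BHS comparison, because a standard CACE needs outcomes for everyone randomised. Similarity on first presentation, gender and age cannot exclude differences in unmeasured prognosis. The Abstract and Discussion speak of refusal only as a cause of underestimation, whereas selection among consenters can act in either direction.

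This should be fixed. The avoidable part concerns secondary outcomes and is a change of wording.

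**What to change.** 1. In Analysis, extend the all-randomised intention-to-treat exception to overall mortality, suicide, and hospital and mental-health service use taken from records. Keep telephone-reported service use in the consented set.
2. First confirm that the ethics approval covers deaths and service use in the records of non-consenters for the planned follow-up. If it does not, state that as the reason for the restriction.
3. Reconcile Analysis with the cost section: say which population the intention-to-treat label means, and which cost components exist only for consenters.
4. Describe the BHS and other questionnaire results as comparisons of consenters, open to bias in either direction, and do not present CACE as a correction for them. Weighting by probability of consent is at most an optional sensitivity analysis, reported as reducing the bias, not removing it.

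The cost is a few sentences, an ethics check and record linkage for patients already being traced for re-presentation. No extra recruitment is needed. Effects on the moved outcomes will be diluted by non-consenters and should be read as effects of being offered the package.
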